##### mHealth-related parameters

2.4.1.3

•**Stability and maintenance:** The number and description of system errors will be recorded.•**Usability:** Usability will be measured with the System Usability Scale (SUS). The SUS provides a simple, fast, and reliable tool to assess usability (15, 16). It comprises 10 statements considering the system evaluated on a five-point rating scale from strongly agree to strongly disagree. The SUS was originally developed by Brooke. It allows to evaluate various systems, including hardware, software, mobile devices, applications, etc (17). In addition, patients will fill in the German version of mHealth App Usability Questionnaire (G-MAUQ) (18). The G-MAUQ is designed to assess usability of mHealth apps and consists of 18 items within three subscales: ease of use, interface and satisfaction and usefulness. Patients can rate each item using a 7-point rating scale (from 1 = disagree to 7 = agree).•**Quality:** The user version of the Quality Assessment of Health-Related Apps (AQUA) (19) consists of 31 items and assesses seven basic dimension of app-quality: usability (4 items), user engagement (5 items), content (4 items), visual design (4 items), therapeutic quality (5 items), impact (4 items), and information (5 items). All items use a five-point rating scale (from 5 = strongly agree to 1 = strongly disagree). For each domain, a sub-score and an overall total score including all domain sub-scores can be calculated.•**Satisfaction:** Patient's subjective satisfaction will be assessed using a 10 mm-visual analogue scale (VAS) from not satisfied at all to extremely satisfied: “How satisfied are you with the application?”.•**User and program experience:** will be evaluated using a customised feedback questionnaire with a five-point rating scale (1 = extremely negative to 5 = extremely positive) including specific questions related to the onboarding procedure, program content, coaching and monitoring. It is aimed to gain further insight of participants' opinion towards the START program. The questionnaire addresses joy, design, understanding, functioning and emotions. Additionally, interaction with the devices (blood pressure measurement device, activity tracker, smartphone or tablet) will be evaluated on a five point-rating scale (from 1 = extremely negative to 5 = extremely positive). Furthermore, patients' experience with the coach will be evaluated (how friendly, competent) using a five-point rating scale (1 = extremely negative to 5 = extremely positive).•**Perceived change:** Patients' subjective global perceived change will be assessed using a visual analogue scale (VAS) from very much worse to very much improved: “How would you rate the change?”.

#### The secondary outcomes comprise the following

2.4.2

•The Functional Independence Measure (FIM) to evaluate the functional status of patients after a stroke throughout the rehabilitation process. It consists of 18 items focusing on motor and cognitive function. Each category is rated on a 7-point rating scale (from 1 = <25% independence to 7 = 100% independence) (20, 21). The FIM score will be used as a descriptive parameter and is used as a standard evaluation at entry to and discharge from the inpatient period.•The Functional Ambulation Categories (FAC) rates ambulation ability, determining how much support a patient requires for walking on a six-point rating scale from zero = unable to walk or assistance by walking through two or more assistants to 5 = able to walk independently everywhere (22).•The Montreal Cognitive Assessment (MoCA) is a screening tool to evaluate mild cognitive dysfunction in different cognitive domains from zero to 30 (no cognitive dysfunction) (23).•The National Institute of Health Stroke Scale (NIHSS) is a widely used tool by health care providers to quantify the impairment caused by a stroke. It consists 11 items, each item scored between zero and four (24). The higher the total score, the more severe the impairment caused by a stroke. NIHSS score will be will be used as a descriptive parameter.•The Modified Rankin Scale (mRS) is a valid and widely used functional measure for patients after a stroke (24, 25). The scale evaluates the degree of disability or dependence in activities of daily living using a rating scale from zero (no symptoms at all) to six (dead).•The Stroke Impact Scale (SIS) is a self-reported questionnaire that evaluates disability and health-related quality of life after a stroke and is designed for repeated administration to track changes over time (26, 27). The SIS consists of eight subscales (strength, hand function, mobility, activity of daily living, emotion, memory, communication and participation) comprising a total of 59 questions. Patients can rate each item on a five-point rating scale (from 1 = could not do at all to 5 = not difficult at all). Final scores range from zero to 100. The SIS includes an extra question on how much the patient feels that she/he has recovered from stroke that is rated on a scale from zero to 100.•The 36-Item Short Form Healthy Survey (SF-36) is a generic patient-reported outcome measure that quantifies health status and measures health-related quality of life (28, 29). It consists of eight subscales (physical functioning, role limitations due to physical problems, general health perceptions, vitality, social functioning, role limitation due to emotional problems, general mental health, and health transition) with eight scales scores, which are the weighted sums of the questions in their subscale (zero to 100). The lower the score the higher the impairment.•The EuroQoL EQ-5D-5l is a patient-reported outcome measure regarding the patients' health-related quality of life (30). It consists of six questions about an individuals' quality of life in general, a visual analogue scale with a score from zero to 100 and descriptive questions about five dimensions: mobility, self-care, activity of daily living, pain and complaints, fear and depression. Each dimension can be evaluated using a five-point rating scale (from 1 = no problems/pain/fear at all to 5 = extreme problems/pain/fear). The descriptive system of the EQ-5D-5l produces a 5-digit health state profile, whereas the value sets are anchored on 11,111 representing complete health.•The German Life-Space Assessment (LSA-G) evaluates the patients' life space and range of mobility. The LSA-G consists of a questionnaire on five different life spaces: rooms besides the bedroom, area outside the house, neighborhood, town or city lived in, outside of the town or city lived in. For each life space individuals are asked whether they visited these spaces and how often, whether they needed assistive devices or personal assistance (31).•The patient's activity level will be assessed using the GENEActiv (Activinsights, Kimbolton, UK) activity tracker. The activity tracker is a lightweight and waterproof raw data accelerometer, designed for health care research and clinical trials. It allows to monitor physical activity, sleep and everyday living through measuring acceleration, posture changes, sleep/wake time, movement activity and intensity. Patients will wear the GENEActiv sensor during inpatient rehabilitation and during the last three weeks of the intervention period. Patients' time spent in different activity levels, steps per day, and energy expenditure will be determined.•An additional measure to evaluate the patients' physical performance is the Short Physical Performance Battery (SPPB) that combines the results of gait speed, chair raise and balance tests (32). The SPPB can be used as a predictive tool for possible impairments and can aid in the monitoring of function in older people. The scores range from zero = worst performance to twelve = best performance.•Blood pressure and heart rate will be measured with a digital blood pressure measurement device (Medisana BU 510, medisana GmbH, Neuss, Germany) provided by the study center. Patients are reminded to measure their blood pressure every morning using the digital blood pressure measurement device and enter their data in the mobile application. During their practice sessions with the therapist (one to three), patients practice the self-measurement. For further practice, patients will be provided a video with the instructions and they can contact their coach if they have questions.•The widely used and well accepted Timed Up and Go (TUG) test will be used to evaluate the patients' mobility and their risk of falling. Patients are asked to stand up from a chair, walk three meters, turn around, walk back and sit down. The time patients need to complete the task will be measured in seconds (33).•The Trunk Impairment Scale (TIS) assesses static (with three items) and dynamic (with four items, each repeated two or three times) sitting balance and trunk coordination (two items, each repeated twice) in sitting position in patients after a stroke (34). Score ranges from zero to 23, where the higher score indicates better balance and coordination.•Furthermore, a weekly reporting scheme will document progress of the investigation, serious and non-serious adverse events and device deficits. Potential harm will be assessed by the following measures: recurrent stroke, serious adverse events (death, life threatening, in-patient hospitalization or prolongation of existing hospitalization, persistent disability).

### Sample size and statistical analyses

2.5

The sample size was defined based on relevant scientific literature that suggests sample sizes ranging between 24 and 50 participants (35, 36) for the justification of a feasibility study. Based on this recommendation, a convenient sample size of 40 patients was determined to cover different stages of the modified Rankin Scale.

Data from all participants will be analyzed quantitatively using JASP (0.18.0, The Jasp Team, Amsterdam, The Netherlands), R Studio (2023.06.0, Posit PBC, Boston, MA, USA) and Microsoft Excel (Excel 2019, Microsoft Corporation, Redmond, WA, USA). No sub-group analysis or interim analysis are planned.

**Primary analyses:** Quantitative data analysis will include descriptive statistics of all primary outcome variables: process-related parameters, training-related parameters and mHealth-related parameters. Raw count (absolute and relative frequencies (n,%) will be presented for count and nominal data, medians (range, 25th and 75th percentiles) will be reported for ordinal data and means (+/- standard deviation) will be reported for continuous data.

The START program on the Blended Clinic platform will be considered feasible and useful if at least half of the following criteria are met:
•Sample size: ≥75% of targeted sample size will be achieved•Recruiting rate: ≥40% of informed patients will be enrolled•Drop-out rate: ≥80% of enrolled patients will complete study participation•Adherence: ≥70% of planned trainings will be completed•Stability and maintenance: ≤3 system failures per week•Safety: number of (serious) adverse events in <10% of all participants•SUS: scores above 70 represent an acceptable usability, with scores smaller than 50 being judged as unacceptable (16)•G-MAUQ: average scoring ≥4•AQUA: average scoring in each dimension ≥3•NPS: average satisfaction ≥50%•Satisfaction (VAS): average satisfaction ≥50%•Perceived change (VAS): health status at least remained the sameSecondary analysis will include descriptive statistics of all secondary outcome variables and pre-post comparisons of clinical and performance-based parameters. Raw count (absolute and relative frequencies (*n*, %) will be presented for count and nominal data, medians (range, 25th and 75th percentiles) will be reported for ordinal data and mean (including standard deviation) will be reported for continuous data. Regarding pre-post comparisons, Wilcoxon signed-rank test will be used for ordinal data and *t*-test for continuous data after testing for normal distribution graphically using QQ-Plot and analyzed using the Shapiro-Wilk test. Significance will be determined with *p*-value of ≤0.05.

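### The feasibility criteria are judged on observed rates and means without any interval, so a result that only just meets a cut-off looks firmer than 30 to 40 patients allow

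*Protocol article*

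**What the plan says.** Section 2.5 (Sample size and statistical analyses) fixes three things.

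- **Sample size.** Literature is cited that "suggests sample sizes ranging between 24 and 50 participants", and from it "a convenient sample size of 40 patients was determined to cover different stages of the modified Rankin Scale". No precision target is given. One feasibility criterion is that "≥75% of targeted sample size will be achieved", which is 30 patients.
- **Primary summaries.** "Quantitative data analysis will include descriptive statistics of all primary outcome variables": counts with percentages, medians with range and quartiles, and means with standard deviations. No interval is listed.
- **Decision rule.** The programme "will be considered feasible and useful if at least half of the following criteria are met". Twelve criteria follow, mostly cut-offs on an observed rate or mean. Two examples are "Drop-out rate: ≥80% of enrolled patients will complete study participation" and "Safety: number of (serious) adverse events in <10% of all participants".

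The same section plans Wilcoxon and t-tests at the 0.05 level, but only for the secondary pre-post comparisons. Section 3.1 (Strengths) gives the results a central part in planning a later randomised trial.

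**The concern.** The article turns descriptive summaries into a verdict but gives the reader no measure of how well each rate is estimated. A completion rate of exactly 80% and one of 95% would both be reported as met, although only the second is good evidence that true completion is at least 80%.

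Recruitment, attrition and adverse-event rates are quantities that a later randomised trial is sized and scheduled from. If a just-met figure is carried forward as though it were known, that trial may be planned with too little allowance for drop-out, too short a recruitment period, or too favourable a view of safety.

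**Working it through.** **Inputs**

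- Target 40, and lowest number that satisfies the sample-size criterion 0.75 × 40 = 30 (section 2.5). The article gives no calculation behind 40, so there is no planned precision to reproduce.
- Cut-offs: completion at least 80% of enrolled patients; patients with adverse events below 10%; enrolment at least 40% of informed patients; adherence at least 70% of planned trainings (section 2.5).
- Recruitment so far: 51 asked, 19 agreed (section 3.3, Trial status).
- Assumption: the safety criterion is read as the proportion of patients with at least one event.

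**Method.** For x of n, the exact (Clopper-Pearson) 95% limits are: lower = 2.5% quantile of Beta(x, n − x + 1); upper = 97.5% quantile of Beta(x + 1, n − x). The chance that a criterion is met under a true rate p is a binomial tail: P(X ≥ cut-off count) for completion and recruiting, P(X ≤ highest passing count) for safety.

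**Exact intervals at the count that only just passes**

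| Criterion | Count | Observed | Exact 95% CI |
|---|---|---|---|
| Completion, n = 40 | 0.80 × 40 = 32 | 80% | 64.4% to 90.9% |
| Completion, n = 30 | 0.80 × 30 = 24 | 80% | 61.4% to 92.3% |
| Adverse events, n = 40 | 3 (4/40 is 10%, fails) | 7.5% | 1.6% to 20.4% |
| Adverse events, n = 30 | 2 (3/30 is 10%, fails) | 6.7% | 0.8% to 22.1% |
| Recruiting, 100 informed (40 enrolled) | 40 | 40% | 30.3% to 50.3% |
| Recruiting, 75 informed (30 enrolled) | 30 | 40% | 28.9% to 52.0% |

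The lower limit for completion lies 80 − 64.4 = 15.6 points (n = 40) or 80 − 61.4 = 18.6 points (n = 30) below the cut-off. For safety the error runs the other way: a met result does not exclude a rate about twice the cut-off. For recruiting the denominator is informed patients, and the lower limit is about 10 points below 40%.

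**The count to date.** 19/51 = 37.3%, exact 95% CI 24.1% to 51.9%. Without an interval this reads as short of 40%; with one, it is compatible with rates on either side.

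**Chance that a criterion is met when the truth is worse than the cut-off**

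| True rate | Larger sample | Smaller sample |
|---|---|---|
| Completion 75% | 30.0% (n = 40) | 34.8% (n = 30) |
| Completion 70% | 11.1% | 16.0% |
| Completion 60% | 0.6% | 1.7% |
| Adverse events 15% | 13.0% (n = 40) | 15.1% (n = 30) |
| Recruiting 35% | 17.2% (100 informed) | 21.4% (75 informed) |

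**Adherence.** Sessions are clustered within patients, so the unit should be each patient's own percentage. The article gives no standard deviation; I assume 20 to 35 percentage points. The half-width is t(0.975, n − 1) × SD/√n. For n = 40: 2.023 × 20/6.325 = 6.4 to 2.023 × 35/6.325 = 11.2 points. For n = 30: 2.045 × 20/5.477 = 7.5 to 2.045 × 35/5.477 = 13.1 points.

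**The case against.** Four arguments stand against the point.

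- **Descriptive analysis is usual in feasibility work, and an unseen full protocol or SAP may add intervals.** This is fair and keeps the point moderate. It does not remove it, because the article itself lays out the primary summaries and a decision rule that uses observed values alone.
- **The rule does discriminate.** A reader might infer that 30 to 40 patients cannot tell acceptable from unacceptable performance. The figures do not support that: true completion of 60% passes in about 1% to 2% of studies, and true completion of 90% passes in 98% (n = 40) or 97% (n = 30). The uncertainty is confined to results near the cut-offs.
- **A pass rate near one half at the cut-off is not a small-sample fault.** A reader might call the verdict a coin toss because true completion of 80% is declared met in only 59% of studies of 40. Any rule on a point estimate behaves this way: the figure is 56% at n = 100, 53% at n = 400 and 51% at n = 4000. This is no argument against the sample size.
- **Requiring the whole interval to clear the cut-off would be too strict.** At n = 40 that needs 38 completers (37/40 has a lower limit of 79.6%), which true completion of 90% would achieve in only 22% of studies. For safety it needs 0/40 (upper limit 8.8%), and at n = 30 even 0/30 (upper limit 11.6%) fails. A formal grading into clearly met, uncertain and not met is therefore not proposed.

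The chance of a wrong overall verdict across the twelve criteria has not been calculated. It would need joint assumptions that the article does not supply.

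**Conclusion.** The point holds as a moderate, inexpensive improvement. Section 2.5 fixes a yes/no verdict on observed values without any statement of precision, and a criterion that is only just met does not exclude clearly worse rates: completion as low as 61% to 64%, adverse events in up to 20% to 22% of patients, and recruiting as low as 29% to 30%.

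The size rests on results close to the cut-offs; 38/40 completers would exclude a rate below 80%. It also rests on 30 to 40 patients contributing to completion and safety, on 75 to 100 informed patients for recruiting, and, for adherence, on an assumed standard deviation. The sample-size and system-failure criteria are not patient proportions and are not affected. The documents do not show that the cut-offs are wrong or that 40 patients is too few for a feasibility study.

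**What to change.** In section 2.5, add to the primary analyses:

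- exact (Clopper-Pearson) 95% intervals for the recruiting rate (denominator: informed patients), for completion, and for the proportion of patients with adverse events;
- t-based or bootstrap 95% intervals for the mean questionnaire and VAS scores, and for adherence computed per patient and then averaged;
- a sentence beside the half-of-criteria verdict that names the criteria whose interval spans the threshold;
- a statement that the intervals, not the point estimates alone, will be used to plan the randomised trial.

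The cut-offs and the half-of-criteria rule can stay as they are. The cost is a few lines of R, which the article already names as analysis software, and no new data. The only downside is a slightly more cautious conclusion.

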### Measurement sessions, outcomes and outcome measures

2.4

Patients will be evaluated during three measurement sessions: before the begin of the START program (T1), at discharge (T4), and after completion of the 12-week program (T6). The 12-week program was implemented for two reasons. Firstly, the greatest functional improvements following a stroke are typically observed during the early subacute phase, particularly within the first three months. Secondly, this period coincides with the transition from inpatient to outpatient care and rehabilitation, which we aimed to support and evaluate. All visits will take place in the rehabilitation center. If it is the patient's wish, the last measurement session can take place at the patients' home. Table 3 provides an overview on all measurement sessions, outcomes and outcome measures.

**Table 3 T3:** Summary of scheduled visits, relevant procedures and duration for patients.

Investigation period	Place of visit	Event	Time point	Content	Duration
Enrolment	Inpatient rehabilitation	Patient information	Day −10 to 0	Study information	10 min
		T0	Day 0	Sign informed consent	5 min
		T1	Day 1–7	Baseline assessment: MoCA, mRS, EQ-5D-5l, SPPB, TUG, TIS	20–30 min
Interventional Phase		T2	Week 1 +/− 7 days	Practice session 1 • Introduction to the application Blended Clinic and the START program • Practice to interact with and navigate through the application menus under supervision • Perform 1 to 8 exercises of training program under supervision • Introduction to self-measurement and entering blood pressure values • Set up activity tracker	30–60 min
		Practice	4–14 days	• Patients practice exercises on their own • Patients wear activity tracker and measure blood pressure • Patients receive about 1 to 5 coaching messages • Patients fill in SIS, SF- 36, mRS	5–10 min per training
		T3	Week 2 +/− 7 days	Practice session 2 • Practice to interact with and navigate through the application menus under supervision • Perform 1 to 8 exercises of training program under supervision	30–60 min
		Optional T3b	Week 3 +/− 7 days	Practice session 3 (optional) • Practice to interact with and navigate through the application menus under supervision • Perform 1 to 8 exercises of training program under supervision	30–60 min
		T4	Discharge from inpatient centre	Patients fill in SIS, SF-36, mRS, LSA-G	30 min

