##### Training-related parameters

2.4.1.2

•**Safety:** (Serious) adverse events and device deficiencies will be recorded.•**Acceptance:** Patients satisfaction will be measured with the Net Promoter Score (NPS) at the end of the intervention. The NPS is widely used for measuring user satisfaction. It involves a single question (“How likely is it that you would recommend START to a friend or colleague?”) with an 11-point rating scale (14).•**Adherence:** The number of completed exercise sessions vs. planned exercise sessions, the duration of completed exercise sessions, the number of completed blood pressure measurements vs. planned measurements and the actual wearing time of the activity tracker vs. the planned wearing time during the pre-defined time period will be recorded.•**Drop-out rate:** The number and reasons for drop-out will be listed and assessed during the entire investigation period. If possible, the reason for withdrawal will be documented in the eCRF.

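### Two of the twelve feasibility criteria are mis-specified: the NPS cut-off is not a Net Promoter Score, and the SUS cut-offs leave 50 to 70 without a verdict

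*Protocol article*

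**What the plan says.** Feasibility is the primary outcome (section 2.4.1). Section 2.5 states that the program "will be considered feasible and useful if at least half of the following criteria are met" and lists twelve criteria without weights. Six rest on study conduct: sample size, recruitment, drop-out, adherence, system stability and safety. Six rest on patients' ratings: SUS, G-MAUQ, AQUA, NPS, satisfaction VAS and perceived-change VAS.

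For the NPS, section 2.4.1.2 (Acceptance) gives a single item, "How likely is it that you would recommend START to a friend or colleague", "with an 11-point rating scale". The criterion in section 2.5 is "NPS: average satisfaction ≥50" per cent.

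For the SUS, section 2.5 says "SUS: scores above 70 represent an acceptable usability, with scores smaller than 50 being judged as unacceptable".

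For the G-MAUQ, rated 1 to 7 in section 2.4.1.3, the criterion is "G-MAUQ: average scoring ≥4". For the AQUA, rated 1 to 5, the average must be at least 3 in each of seven dimensions.

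**The concern.** A criterion that is counted towards a verdict needs one pass mark, on the scale of the instrument it names. Two of the twelve lack this.

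- **NPS.** The named score is a net of promoters and detractors, while the criterion is an average. The 50% can be read as a mean of 5 out of 10 or as a net score of 50, and these are very different bars. The criterion is also labelled satisfaction, although the item asks about recommending and a separate satisfaction VAS has its own criterion with the same threshold.
- **SUS.** A result from 50 to 70 is neither acceptable nor unacceptable, so nobody can say whether the criterion is met. The criterion also does not say that it applies to the mean, as most of the other rating criteria do.

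With a simple count and a bar of six, one undecided criterion can settle the primary conclusion, and section 3.1 says the results will guide a randomized trial. The choice would then fall to whoever analyses the data, after the ratings are known.

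**Working it through.** The plan prints no figure to reproduce here. N = 40 is a convenience number and the cut-offs are given without derivation, so the check is on the cut-offs themselves.

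**Inputs.** The twelve criteria and the at-least-half rule come from section 2.5, and the scale ranges from sections 2.4.1.2 and 2.4.1.3. Two things are assumed from the standard definitions of the named instruments, because the article does not print them: the 11 points run from 0 to 10 with NPS = % scoring 9-10 minus % scoring 0-6, and SUS = 2.5 × the sum of item contributions, with five positively and five negatively worded items.

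**Number needed.** 12 / 2 = 6.

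**NPS, mean against net score.**
- All patients answer 5: mean 5/10 = 50%, which passes. NPS = 0 - 100 = -100.
- All patients answer 6: mean 60%, which passes. NPS = 0 - 100 = -100.
- Highest net score at a mean of 5: a share p answers 9 and the rest 0, so 9p = 5 and p = 5/9. NPS = 100 × (5/9 - 4/9) = +11. At a mean of exactly 5, the net score therefore lies between -100 and +11.
- Lowest mean at a net score of 50: put promoters at 9, passives at 7 and a share d of detractors at 0. Promoters are 0.5 + d and passives 0.5 - 2d. Mean = 9(0.5 + d) + 7(0.5 - 2d) = 8 - 5d. The largest possible d is 0.25, giving 8 - 1.25 = 6.75.

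No sample with a mean of 5 or 6 can have a net score of 50, so the two readings of the cut-off are incompatible.

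**SUS at all-neutral answers.** 2.5 × [5 × (3 - 1) + 5 × (5 - 3)] = 2.5 × 20 = 50. This is not below 50 and not above 70, so it has no verdict.

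**Position of the other cut-offs.** G-MAUQ: (4 - 1)/(7 - 1) = 50% of the range. AQUA: (3 - 1)/(5 - 1) = 50% of the range. Both use ≥, so a mean exactly at the midpoint passes.

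**Criteria met when every patient gives the midpoint answer on all six rating scales and no other criterion is met:**

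| Reading of the NPS criterion | SUS 50-70 not met | SUS 50-70 met |
|---|---|---|
| Mean ≥ 50% | 5 | 6 |
| Net score ≥ 50 | 4 | 5 |

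The verdict needs 6. Only the most lenient pair of readings reaches it, and in that cell sample size, recruitment, drop-out, adherence, stability and safety could all have failed.

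**The case against.** The strongest reply is that the intended meaning is not hard to guess and that a descriptive, single-arm feasibility study may set modest bars. In a list of criteria to be met, above 70 reads naturally as the SUS pass mark, with below 50 as a descriptive label. The NPS cut-off may be a loosely worded net score of 50, which would be demanding. Section 2.4.1.2 does present the NPS as the protocol's satisfaction measure, so the label has a source. All primary variables will be reported descriptively, so a poor result would remain visible.

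Much of this stands, and it limits the point to wording. It does not remove the point: the word average points to a mean, the percentage fits both readings, and the rule counts criteria as met or not met.

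A reader might go further and infer that indifferent users make the program a success. The documents do not support that:
- Uniform midpoint answers meet five criteria, one short, unless SUS 50-70 is counted as met. The SUS gap leaves a verdict open; it does not itself reward indifference.
- AQUA must reach 3 in all seven dimensions. If answers scatter around neutral, each dimension mean has about an even chance of reaching 3. All seven then do so with probability 0.5^7 = 0.8% if independent, and about 37% in a simulation with an assumed correlation of 0.95.
- The satisfaction VAS runs from no satisfaction to extreme satisfaction, so its centre is moderate satisfaction, not indifference.
- Perceived change at least the same is a defensible no-deterioration bar. Section 2.4 does say that "the greatest functional improvements following a stroke are typically observed during the early subacute phase", which makes the bar easy to meet, but that sentence is about typical functional course and does not show that patients will report no worsening.

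**Conclusion.** The point holds for two of the twelve counted criteria. The NPS criterion does not match the instrument it names: a mean of 5 or 6 out of 10 passes while the net score can be -100, and a net score of 50 would need a mean of at least 6.75. The SUS criterion has no verdict from 50 to 70.

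The effect on the primary conclusion is bounded. Under uniform midpoint answers the count ranges from 4 to 6 according to how these two criteria are read, against 6 needed. That is a limiting case, not a forecast, and it rests on the standard NPS and SUS scoring rules. The midpoint cut-offs for G-MAUQ and AQUA are a secondary matter of interpretation. How high such bars should be in a feasibility study is a design judgement, and nothing in the document makes them errors.

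**What to change.** Before the T6 ratings are analysed, and without reference to any already collected:

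1. **NPS.** Define the criterion as a net score, state the scoring and state the cut-off. Alternatively keep the average, call it a mean recommendation rating with its cut-off in scale points, and stop calling it NPS or satisfaction. The choice of cut-off is the sponsor's.
2. **SUS.** State that the criterion is met only if the mean score is above 70. The band below 50 can stay as a descriptive label.
3. **G-MAUQ and AQUA.** Leave the cut-offs, but note when the count is interpreted that means exactly at the scale midpoint pass.

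The number of criteria stays at twelve, so the bar of six does not move. Questionnaires and visits are unchanged. The cost is a small, dated wording change to a protocol that already has ethics and authority approval and is recruiting, and slightly less favourable pass rates.
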